## Abstract

**Background:**

Inpatient psychiatric care is a scarce and expensive resource in the National Health Service (NHS), with chronic bed shortages being partly driven by high re-admission rates. People often need to go to a hospital when they have a mental health crisis due to overwhelming distressing psychotic symptoms, such as hearing voices (hallucinations) or experiencing unusual beliefs (delusions). Brief talking therapies may be helpful for people during an acute inpatient admission as an adjunct to medication in reducing re-admission rates, and despite promising findings from trials in the USA, there have not yet been any clinical trials on this kind of intervention within NHS settings.

**Methods/design:**

The amBITION study is a feasibility randomised controlled trial (RCT) of a manualised brief talking therapy (Mindfulness-Based Crisis Intervention (MBCI)). Inpatients on acute psychiatric wards are eligible for the study if they report at least one positive psychotic symptom and are willing and able to engage in a talking therapy. In addition to treatment as usual (TAU), participants will be randomly allocated to receive either MBCI or a control intervention (social activity therapy (SAT)) which will be based on doing activities on the ward with the therapist. The primary objective of the study is to find out whether it is possible to carry out this kind of trial successfully within UK inpatient settings and to find out whether patients and staff find it an acceptable intervention. The secondary objective is to collect pilot data on primary and secondary outcome measures, including re-admission rates at 6-month follow-up. This will provide information on the appropriateness of re-admission as the primary outcome measure for future efficacy trials, as well as data on the acceptability and utility of the clinical self-report measures.

**Discussion:**

The results of the feasibility trial will indicate whether a subsequent efficacy pilot trial is warranted and, if so, will provide vital information for the planning of such a trial (e.g. pilot data on expected effect sizes). If future research finds that MBCI is an effective and safe intervention, then patients will benefit from access to better treatment within inpatient care which would reduce re-admission rates. This trial therefore addresses an area of urgent concern for service users, clinicians and the wider NHS.

**Trial registration:**

Current controlled trials ISRCTN37625384

## Background

People often need to go to a hospital when they have a mental health crisis due to overwhelming distressing psychotic symptoms, such as hearing voices (hallucinations) or experiencing unusual beliefs (delusions). However, inpatient care is the most costly, and over-subscribed, form of care provided by NHS mental health trusts. Mental health trusts across the United Kingdom (UK) can neither afford, nor physically accommodate, all the patients requiring admissions [1]. Reducing admission rates is therefore an area of urgent priority given on-going bed closures, with a recent study reporting a 62 % reduction in psychiatric beds nationwide from 1988 to 2008 [2]. Psychological interventions are well-established in their efficacy for reducing psychotic symptoms that have not responded adequately to pharmacological intervention [3]. However, most therapy trials in the UK have been conducted in outpatient settings, with therapy lasting approximately 6 months [4]. There is a dearth of robust evidence for the feasibility and efficacy of brief psychological interventions exclusively within acute inpatient settings. This could be due to unfounded assumptions that inpatients are always too unwell to make use of therapy or that therapy always has to be lengthy to be of any benefit. However, this may represent a missed opportunity to engage patients in psychological therapies at a critical point in the care pathway, using crisis-focused interventions. When people are admitted to a hospital at times of crisis, this can be an ideal time to offer psychological interventions as problematic thoughts, feelings and behaviours are readily accessible and the inpatient setting provides wider support. Two research studies conducted in the USA have investigated brief psychological interventions for inpatients with psychotic symptoms [5, 6]. Participants received between one and five individual sessions of an acceptance-based therapy known as acceptance and commitment therapy (ACT). Brief crisis-focused interventions target risk of future relapse and re-admission by seeking to help a person understand how their existing coping strategies have brought them into crisis and to develop skills in alternative coping strategies. ACT interventions aim to increase what is termed *psychological flexibility*, defined as “the ability to contact the present moment more fully and without needless defence” [7]. Patients’ existing coping strategies are often lacking in psychological flexibility, relying instead heavily on experiential avoidance (i.e. attempts to avoid unwanted thoughts, feelings or sensations) [8]. For example, a study of 50 patients experiencing voices in the context of a psychotic illness found that being less accepting towards internal experiences was positively associated with behavioural attempts to resist voices [9]. For example, people may cope with unpleasant auditory hallucinations by drinking alcohol or using illicit drugs in an attempt to block them out. Someone experiencing persecutory delusions may choose to avoid the anxiety they feel when they go out in public by isolating themselves at home. These behaviours not only stop the person from being able to function normally in their everyday life but also increase the risk of serious self-neglect and re-admission. ACT therefore aims to help people to accept symptoms, rather than trying to avoid or eliminate them, and to defuse or step back from them, while promoting behaviours which are consistent with the person’s underlying values and goals in life [7]. This acceptance-based approach is also consistent with Chadwick’s model of mindfulness for psychosis, in which people are taught skills in relating mindfully to psychotic symptoms, as an alternative to either experiential avoidance or simply getting lost in struggle and rumination [10].

The two USA studies found that the intervention was successful in reducing re-admission rates at 4-month follow-up. Bach and Hayes reported that the re-hospitalisation rate of the ACT group was half that of the treatment as usual (TAU) group (20 vs. 40 % respectively), a statistically significant difference. Gaudiano and Herbert (2006) reported the same trend (28 % ACT vs. 45 % TAU respectively), but these results did not reach statistical significance. It is not yet known whether such brief crisis-focused interventions would translate effectively to NHS inpatient care in the UK. As brief crisis-focused psychological interventions have not been subject to controlled trials in the UK, this study will be a feasibility trial providing valuable data to inform possible later efficacy pilot trials (BrIef Talking therapIes ON wards (amBITION) study). A brief, manualised therapy (Mindfulness-Based Crisis Intervention (MBCI)) will be compared with an active control condition (social activity therapy (SAT)) to help account for non-specific elements of therapy, such as having individual attention from an empathic therapist.

The primary objective of the study is to find out whether it is possible to carry out this kind of trial successfully within inpatient settings and to find out whether patients and staff find it an acceptable intervention. The secondary objective is to collect pilot data on primary and secondary outcome measures.

## Methods/design

### Study design and timeline

This study is a single-centre, parallel-groups, feasibility randomised controlled trial. Trial procedures and the assessment schedule are shown in the study plan (Fig. 1). In brief, service use data (re-hospitalisation rate, use of crisis team, relapse rate) will be collected using case note review at 3- and 6-month follow-up. Self-report clinical measures will be taken at baseline, post-therapy and at 3-month (mid-point) and 6-month follow-up after discharge (end-point). The 3-month mid-point follow-up was included in order to minimise missing data arising from loss to follow-up and to provide more detailed information on symptom change in the short-term after discharge. The service use data will provide information on the appropriateness and sufficiency of re-admission as the primary outcome measure for future efficacy trials or whether an additional primary outcome would be indicated (e.g. relapse rate from case note review). The trial will also provide important data on the acceptability and utility of the self-report clinical measures, for example, whether participants are willing and able to complete the measures and whether they show sensitivity to change over time.

**Fig. 1 Fig1:**
[figure not shown]
Study plan

### Study population

#### Inclusion criteria

i)Aged 18 or aboveii)Current psychiatric inpatient on a working-age adult wardiii)Diagnosis of schizophrenia-spectrum disorder or psychotic symptoms in the context of an affective disorder (ICD-10 codes F20-39; [11])iv)Reports at least one current positive psychotic symptom (scores >1 on frequency on self-report symptom scale)v)Able to give informed consent to participate in trial, as assessed by consultant psychiatrist/responsible clinicianvi)Willing and able to engage in psychological therapy

#### Exclusion criteria

i)Established diagnosis of learning disability or major cognitive impairment arising from any underlying medical condition (e.g. head injury, neurological disorder) resulting in significant functional impairmentii)Unable to engage in a talking therapy in English or to complete simple written questionnaires in Englishiii)Primary diagnosis of substance misuseiv)Lacks capacity to consent to participation in research trialv)Unable to take part in individual therapy due to risk of aggression/violencevi)Mental state precludes possibility of engaging in a talking therapy, e.g. significant thought disorder

#### Recruitment, randomisation and blinding

Patients will be recruited from acute inpatient psychiatric wards from a large mental health trust in South London, serving a local population of 1.1 million people, with approximately 6000 acute inpatient admissions a year. Potentially eligible patients will be identified by their inpatient care team and will be approached to take part by the researcher with permission of their inpatient Consultant Psychiatrist and primary nurse. Patients may take part in the trial if they are admitted under a section of the Mental Health Act (MHA) so long as they are deemed to have retained capacity to consent to participation in research. Further eligibility screening by reference to electronic clinical notes will be conducted with written consent from patients who have been approached and are potentially interested in participating. Patients will be given a copy of the brief patient leaflet at this point to introduce them to the main aims of the study. Once the researcher has confirmed the patient’s eligibility, she will approach the patient again to give them a copy of the full patient information sheet and to talk it over with them and explain the study further. Patients will be given sufficient time (at least until the next day) to read over the information, think it over, ask questions and to discuss their participation with anyone they may wish to (e.g. primary nurse, family member). After giving informed consent, eligible participants will first complete baseline measures and then be randomised using a computerised service at the Kings Clinical Trials Unit (KCTU). Due to the nature of the intervention, blinding of participants and therapist is not possible. The participant’s inpatient and community care team will however be blinded to treatment allocation, as far as possible. Conservative measures will be used such as not referring to any content of the therapy sessions in clinical notes and conducting all therapy sessions in a private room on the ward. The two therapies will be referred to by neutral labels in all participant and staff literature (therapy 1 vs. therapy 2) in order to promote equal treatment credibility between the conditions. Block randomisation will be used, with randomly varying block sizes to ensure allocation concealment. As this is a feasibility trial, the primary outcomes relate to feasibility data rather than clinical outcomes. PJ will be primarily responsible for gathering all trial data and will not be blinded to treatment condition, but some follow-up data may also be collected wherever possible by appropriately trained staff independent of the clinical team (e.g. research nurse, postgraduate students). The study will be conducted in line with Good Clinical Practice (GCP) guidelines for clinical trials [12]. The data management plan includes standard procedures such as the use of anonymous identification codes.

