#### Mindfulness-Based Crisis Interventions (MBCI)—experimental intervention

MBCI was developed in line with the model of mindfulness for psychosis proposed by Chadwick [10]. People who experience positive psychotic symptoms (e.g. voices, paranoid thoughts) often respond by trying to avoid experiences (experiential avoidance) or at the other end of the spectrum, by getting lost in engaging with them (rumination, confrontation). Mindfulness offers an alternative way of responding, with acceptance and non-judgemental awareness in each moment, allowing psychotic symptoms to move in and out of awareness without the person getting caught up in struggling against them. The treatment protocol for the current trial was adapted for use within an acute crisis setting, partly based on PJ’s clinical experience of working within inpatient settings and in consultation with ACT experts in the USA, including the lead author of one of the key inpatient trials [6].

There are three key components to be included in each session:i.Developing mindfulness skills (guided practice)ii.Making sense of crisis using mindfulness modeliii.Identifying values and setting goals

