A typical session will start with a 5-min mindfulness practice, including frequent guidance that includes reference to psychotic experience and uses everyday, concrete language. The therapist will then move on to developing a collaborative understanding with the participant of what has brought them to a hospital on this occasion, focussing on how they usually try to cope with difficult voices, thoughts, feelings and experiences and how well these strategies are working for them. Given the time constraints, therapists will share a formulation and example strategies (following Chadwick [10]), asking the participant to connect with and provide examples of his or her own habitual reactions. In line with the formulation, the therapist will highlight the participant’s attempts to either block out, suppress or otherwise escape from unwanted internal experiences or reactions that mean getting caught up in struggling with internal experiences (rumination, fighting). Mindfulness is located as a middle way between these two reactive styles. Finally, the therapist will work with the participant to identify their values (e.g. family, work, health, society) and discuss specific behavioural goals consistent with these values. Participants are then helped to set a small, achievable goal for homework at the end of each session which can be reviewed at the beginning of next session, where possible. In preparation for discharge, longer-term goals can also be identified (e.g. starting a college course) and will be shared with the community care team at the end of therapy, to act as a bridge to carrying on the recovery process in the community.

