#### Secondary objective—pilot data

Pilot outcome measures (service use and clinical measures) will be collected, as detailed in Table 1. A cost-effectiveness analysis of the intervention is outside the scope of this feasibility study; however, the service-use data collected would be relevant to the future assessment of economic costs. This is in addition to data on therapy costs which will be collected, such as the average number of sessions received per participant.

**Table 1 Tab1:** Summary of outcome measures

Pilot data—inpatient/crisis service use			
Outcome		Method	Time period
Primary outcome:			
1) Re-hospitalisation (≥1 OBD)		Clinical notes	Discharge—3- and 6-month follow-up
Secondary outcomes:			
2) Time to re-admission (days)		Clinical notes	Discharge—3- and 6-month follow-up
3) Total number of OBDs		Clinical notes	Discharge—3- and 6-month follow-up
4) Episodes of care with crisis/home treatment team		Clinical notes	Discharge—3- and 6-month follow-up
5) Contact with CMHT (number of meetings/contact with CMHT including care co-ordinator)		Clinical notes	Discharge—3- and 6-month follow-up
6) Reference to therapy goal which was shared with team		Clinical notes	Discharge—3- and 6-month follow-up
7) Relapse rate		Clinical notes	Discharge—3- and 6-month follow-up
Pilot data—clinical measures			
Construct assessed	Questionnaire	Method	Time points
Credibility of therapy	1) Therapy credibility	Self-report	Baseline only (immediately post-randomisation)
In the moment rating of stress and interference from symptoms and hope for the future	2) Stress bubbles	Self-report	At the beginning and end of every therapy session
Frequency, distress and believability of most distressing symptom	3) Self-ratings of psychotic symptoms (based on Bach and Hayes, 2002; Gaudiano and Herbert, 2006)	Self-report	Baseline, end of therapy, 3-month mid-point and 6-month follow-up
Mood—depression, anxiety and stress	4) DASS-21 (Depression, Anxiety and Stress Scale; Lovibond and Lovibond, 1995)	Self-report	Baseline, end of therapy, 3-month mid-point and 6-month follow-up
Self-defined recovery	5) QPR (Questionnaire about the Process of Recovery; Neil et al 2009)	Self-report	Baseline, end of therapy, 3-month mid-point and 6-month follow-up
Voices (incl. frequency, distress, interference and compliance)	6) HPSVQ (Hamilton Program for Schizophrenia Voices Questionnaire; Van Lieshout and Goldberg, 2007)	Self-report	Baseline, end of therapy, 3-month mid-point and 6-month follow-up

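### Planned sharing of MBCI goals with the community care team conflicts with the claim that this team is blinded, and Table 1 item 6 has no evident SAT counterpart

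*Protocol article*

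**What the plan says.** Under Recruitment, randomisation and blinding, the article accepts that participants and therapist cannot be blinded, but states that the participant's "inpatient and community care team will however be blinded to treatment allocation, as far as possible". The supporting measures are "not referring to any content of the therapy sessions in clinical notes", holding sessions in a private room, and neutral naming: "The two therapies will be referred to by neutral labels in all participant and staff literature".

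In the MBCI section, "Identifying values and setting goals" is one of three key components of each session. The section continues: "In preparation for discharge, longer-term goals can also be identified", and these "will be shared with the community care team at the end of therapy, to act as a bridge to carrying on the recovery process".

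The SAT section describes choosing and doing enjoyable activities with a supportive therapist who uses no model-specific technique. It mentions no values work, no longer-term goals and no communication to the community team.

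Table 1, under Secondary objective—pilot data, lists as secondary outcome 6 "Reference to therapy goal which was shared with team". The source is clinical notes and the period runs from discharge to the 3- and 6-month follow-ups. The entry is not limited to one arm.

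**The concern.** The group declared blinded is also the group that one arm's therapy is designed to inform. The disclosure is a scheduled step of MBCI, not an accidental leak, and the outcome table relies on it having happened.

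Three things are at stake:

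- **Service-use comparisons.** Re-hospitalisation (the pilot primary outcome), crisis-team episodes, contact with the community mental health team (CMHT) and relapse are all read from clinical notes. The Analysis plan compares time to re-admission formally between arms. A reader who takes the blinding statement at face value would assume that community staff did not know the allocation.
- **The assessment of blinding.** The article lists staff feedback on blinding procedures among its acceptability data, so whether blinding works is part of the primary objective.
- **Item 6.** If goals are shared in one arm only, a between-arm comparison of how often they are mentioned has no meaning.

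**Working it through.** The article gives no figure on this point, so the check sets the sections against each other.

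1. **Is a goal session content?** Yes. Goal setting is one of the three components of each MBCI session.
2. **Does the community team receive it?** Yes, where a longer-term goal exists. The MBCI section says that these goals "will be shared with the community care team at the end of therapy".
3. **Is there a SAT equivalent?** None is described. SAT participants choose activities, and the SAT section has no end-of-therapy communication. MBCI-only sharing is therefore an inference from what the two descriptions contain. No sentence excludes sharing in SAT.
4. **Does this meet the blinding statement head-on?** For the community team, yes. The notes rule withholds session content, while the MBCI section passes one element of that content to the same team. Neutral labels do not help if a goal arrives for one label only. For the inpatient team, no: the article describes no goal being sent to it.
5. **Can item 6 coexist with the notes rule?** Only on a narrow reading. Item 6 is non-zero only if someone writes about the shared goal in the notes. If the rule binds the trial therapist alone, a later entry by community staff does not breach it. That entry still presupposes that the team was told the content.
6. **How many participants?** The target is 60, with 30 per arm. Longer-term goals can, but need not, be identified, and the number of sessions ranges from one to five depending on length of admission. If k MBCI participants have a goal shared, k lies between 0 and 30. The ceiling is 30/30 of the MBCI arm, or 30/60 = 50% of the trial. The article gives nothing from which to estimate k.
7. **What does item 6 give by arm?** If sharing is MBCI-only, the SAT count is 0/30 because there is no goal to mention. Any non-zero MBCI count m/30 would then give a difference of m/30 − 0/30 = m/30, which reflects the definition and not a treatment effect.
8. **Would the staff feedback detect the unmasking?** The Qualitative data on acceptability section invites staff from the inpatient units where patients were recruited. Community staff are not mentioned, so the feedback as described speaks to inpatient blinding and not to the team that receives the goals.

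**The case against.** The best case for the plan has five parts.

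- **The claim is already qualified by the words as far as possible.** That covers leaks that cannot be prevented. It does not naturally cover a disclosure that the plan itself schedules in one arm.
- **MBCI-only sharing is not stated.** This stands as a limit. The article condenses a fuller protocol, and SAT communication could be described there. But if SAT goals are also shared, the SAT section and item 6 should say so.
- **A goal need not reveal the arm.** The article's example, starting a college course, contains no mindfulness content, and a team would have to know that only one therapy sends goals. This stands. Receipt can unmask, but it does not do so with certainty, and the absence of a goal does not prove SAT.
- **Acting on a goal is treatment, not bias.** Largely right. The article presents goal sharing as a bridge into community recovery, so extra contact prompted by a goal is partly an intended MBCI effect. Only a change in behaviour caused by knowing the allocation would be bias, and the data cannot separate the two.
- **The consequence is limited.** The main outcomes are feasibility outcomes, hypothesis tests are labelled preliminary, and the main data collector is openly unblinded. This limits the harm to the pilot comparisons and to the assessment of blinding. It does not remove the contradiction.

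**Conclusion.** The concern holds for the community team. The article claims that this team is blinded, plans to send it MBCI goals, describes nothing similar for SAT, and counts mention of those goals as an outcome in both arms. Up to 30 participants could be unmasked to the community team; the actual number cannot be derived. Item 6 has no evident SAT counterpart and cannot serve as a between-arm outcome.

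The conclusion rests on one main assumption, that goal sharing is confined to MBCI. That the community team's conduct can affect contact and re-admission is a reasonable inference, which the article does not state.

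A reader might infer more, and the article does not support it:

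- **That blinding fails for every MBCI participant.** Not all need have a longer-term goal, and not every goal identifies the arm.
- **That inpatient blinding fails too.** Nothing described contradicts it.
- **That the re-admission comparison is shown to be biased.** Part of any effect through a shared goal is intended treatment, and no direction or size of bias can be derived.
- **That the blinding procedures go untested.** The staff feedback can still inform on the inpatient team.

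**What to change.** Reconcile the blinding section, the MBCI and SAT descriptions and Table 1, and state whether goals are shared in one arm or both.

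If sharing is MBCI-only:

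- Limit the blinding claim to the inpatient team and state that the community team is not reliably blinded.
- Present goal sharing as part of the MBCI package, and interpret the service-use outcomes, notably CMHT contact and re-admission, with that in mind.
- Interpret the staff feedback on blinding as evidence about the inpatient team.
- Report item 6 as an MBCI-only process measure, with the number of participants who had a goal shared as its denominator.

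The cost is a few sentences of protocol wording and a count of shared goals. The article gives the trial status as in preparation, so the change can be made before recruitment.

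An alternative is a same-format, neutrally labelled summary to the community team in both arms. It is not free: it adds a step to SAT and so alters the control condition. It is suitable only if the sponsor accepts that change. Asking care co-ordinators to guess the allocation would be an optional extra, and a guess made at 6 months could be coloured by how the participant had fared.
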